## Abstract

**Background:**

The COVID-19 pandemic undermined gains in reducing maternal and perinatal mortality in South Africa. The Mphatlalatsane Initiative is a health system intervention to reduce mortality and morbidity in women and newborns to desired levels.

**Objective:**

Our evaluation aims to determine the effect of various exposures, including the COVID-19 pandemic, and a system-level, complex, patient-centered quality improvement (QI) intervention (the Mphatlalatsane Initiative) on maternal and neonatal health services at 21 selected South African facilities. The objectives are to determine whether Mphatlalatsane reduces the institutional maternal mortality ratio, neonatal mortality rate, and stillbirth rate (objective 1) and improves patients’ experiences (objective 2) and quality of care (objective 3). Objective 4 assesses the contextual and implementation process factors, including the COVID-19 pandemic, that shape Mphatlalatsane uptake and variation.

**Methods:**

This study is an implementation science type 2 hybrid effectiveness, controlled before-and-after design with quantitative and qualitative components. The Mphatlalatsane intervention commenced at the end of 2019. For objective 1, intervention and control facility-level data from the District Health Information System are compared for changes in institutional maternal and neonatal mortality and stillbirth rates and associations with QI, the COVID-19 pandemic, and both. This first analysis includes data from 18 facilities, regardless of their allocation to intervention or comparison, to obtain a general idea of the effect of the COVID-19 pandemic. For objectives 2 to 3, data collectors abstract data from maternal and neonatal records, interview participants, and conduct neonatal facility assessments. For objective 4, interviews, program documentation, surveys, and observations are used to assess how contextual factors at the macro-, meso-, and microlevels explain variation in intervention uptake and outcome. The intervention dose is measured at the microlevel only in the intervention facilities. The study assesses the Mphatlalatsane Initiative from 2020 to 2022.

**Results:**

From preliminary analysis, across the 3 provinces, maternal and neonatal deaths increased during the COVID-19 pandemic, whereas stillbirths remained unchanged. Maternal satisfaction with quality of care was >90%. The COVID-19 pandemic severely disrupted the QI teams functioning. However, the QI teams regained their pre–COVID-19 momentum by adapting the QI model, with advisers providing mentoring and support. Variation in adoption at the mesolevel was related to stable and motivated leadership (particularly at the facility level), poor integration into routine processes, and buy-in from senior district managers who were affected by competing priorities. Varying referral and specialist outreach systems, staff availability and development, and service delivery infrastructure are plausible factors in variable outcomes.

**Conclusions:**

Few evaluations rigorously evaluated the effect of health system interventions on improving health services and outcomes. Results will inform the scaling up of successful intervention components and strategies to mitigate the effects of the COVID-19 pandemic or similar emerging epidemics on maternal and neonatal mortality.

**International Registered Report Identifier (IRRID):**

DERR1-10.2196/42041

## Introduction

### Background

The emergence of COVID-19 caused by SARS-CoV-2 in 2020 had a detrimental effect on maternal and infant health gains. Pregnant and breastfeeding women are at a high risk for COVID-19–related morbidity and mortality [1,2]. Given the high number of pre–COVID-19 medically complicated pregnancies in low- and middle-income countries, the pandemic substantially increased the risks to pregnant and breastfeeding women and their infants [3] and undermined gains made in reducing maternal and perinatal mortality [4].

South Africa invested in improving sexual, reproductive, maternal, and neonatal health (SRMNH) services but did not reach the Millennium Development Goals targets for maternal and child health by the end of 2015. Aligned with the United Nations Sustainable Development Goals (SDG) of reducing maternal mortality to <70 per 100,000 live births and neonatal mortality to 12 deaths per 1000 live births [5], South Africa aims to reduce the institutional maternal mortality ratio (iMMR), neonatal mortality, and stillbirths by 50% by 2030 [6]. In 2019, the iMMR of 120 per 100,000 live births was well above the SDG target [6]. Moreover, although the institutional neonatal mortality rate (12 per 1000 live births in 2021) meets the SDG, almost 50% of neonatal deaths are avoidable (2021) [6]. This is despite the substantial reduction in iMMR since 2011, attributable to South Africa’s antiretroviral treatment program, which increased access to lifelong maternal antiretroviral treatment at higher CD4 cell counts [7].

National policies and strategies for SRMNH have been in place but lack a cohesive quality improvement (QI) strategy. These challenges have been exacerbated by the COVID-19 pandemic, which has complicated access to health care and delivery of maternal and perinatal interventions [4]. Furthermore, despite the strengths of South Africa’s existing maternal, perinatal, and child mortality audits, the availability of real-time data to address frontline challenges is undermined by outdated software and fragmented systems with inherent data quality issues and data gaps. These data gaps became more apparent as the pandemic necessitated rapid access to real-time maternal and perinatal data on COVID-19.

Optimal health care provides quality services that are effective and safe while also being timely, equitable, integrated, and efficient [8], with a focus on people-centered care as an essential component [9]. Quality of care is defined as the extent to which health services can increase the probability of desired health outcomes [10].

QI interventions in low- and middle-income countries have improved access to care, skilled delivery, and viral load monitoring. In a South African stepped-wedge randomized controlled trial, a continuous QI intervention resulted in a notable rise in viral load monitoring (relative risk [RR] 1.38, 95% CI 1.21-1.57; *P*<.001) [11]. However, there was no improvement in repeat HIV testing (RR 1.00, 95% CI 0.88-1.13; *P*=.96). In Ethiopia, there was a favorable effect on health workers’ adherence to safe childbirth practices immediately after birth (β=8.22, 95% CI 5.15-11.29) [12]. In Ghana, a QI intervention to reduce waiting time for emergency obstetric care and hand hygiene in the neonatal intensive care unit (ICU) improved hand hygiene compliance by 93%. Moreover, the percentage of mothers needing emergency cesarean surgery with unacceptable waiting times decreased by 4 times, and 93% of the sickest mothers were correctly identified [13].

Conversely, in 2 randomized controlled trials conducted at the primary care level in Nigeria and Malawi, continuous QI was ineffective [14,15]. The researchers rigorously measured continuous QI in terms of impact on neonatal and perinatal mortality rates in the Malawi study [14] and 6-month postpartum retention in the Nigerian study [15]. However, these end points do not reflect the QI activities that occurred in the primary care centers. The variability of these end points is likely related to elements outside the remit of the QI, such as emergency care availability, road infrastructure, and mothers’ educational attainment.

In 2017, the Mphatlalatsane Initiative was launched to provide a national unified response to improve the quality and equity of SRMNH care at the cusp of the National Health Insurance reform, using the Institute for Health Improvement QI methodology [16]. The final output is anticipated to be a proven and replicable model of catalytic health systems and clinical interventions to reduce unintended pregnancies and maternal and newborn deaths. These can be tested for sustainability and scaled up to emulate achievements across the rest of the country.

In this study, we report the protocol for the evaluation of the Mphatlalatsane Initiative. The initial aim of the protocol was to determine if a complex area–based QI initiative would reduce iMMR, neonatal mortality, and stillbirth rate by 50% in 5 years. Given the emergence of COVID-19 in March 2020 in South Africa with concomitant increased public health measures and national level-5 lockdown [17], the Mphatlalatsane Initiative was adapted to provide the much-needed support for maternal and perinatal care during the pandemic. The evaluation protocol was reframed to account for these adaptations and to determine the effect of the Mphatlalatsane Initiative on maternal and perinatal health care and outcomes, implementation processes, and health care system functioning during the pandemic from 2019 to 2022.

### Study Aims and Objectives

The evaluation primarily aims to measure the effectiveness of the Mphatlalatsane Initiative on iMMR, neonatal mortality rate, and stillbirth rate (objective 1). We also assess whether patients’ experiences of care (objective 2) and quality of maternal (objective 3a) and neonatal care (objective 3b) were affected by the pandemic. Objective 4a explores the macrolevel (regional and national) and mesolevel (subdistrict and district) factors, and objective 4b explores the microlevel (facility) process and contextual factors, including the COVID-19 pandemic, to explain variations in QI uptake and program outcomes and implications for scale-up. Partner interviews (objective 4a) commenced in early 2020, and data collection for objective 4b began in May 2021.

### Outcome Measures

The primary end points are (1) iMMR, (2) neonatal mortality rate, and (3) stillbirth rate. The secondary end points include patient experiences of health care quality and facility processes during the antenatal and postpartum periods (objective 2) and the quality of maternal (objective 3a) and neonatal care (objective 3b). The study also explores *macro-, meso-, and microlevel contexts* and implementation processes for improved quality and outcomes of maternal and neonatal health (MNH). Additional details on the secondary outcomes are provided in Multimedia Appendix 1.

## Methods

### Study Setting

The evaluation is underway in 4 intervention and 3 nonoverlapping comparison districts across 3 provinces: the Eastern Cape, Limpopo, and Mpumalanga. All catchment areas are in 1 district, except for the Eastern Cape intervention catchment area, which spans across 2 districts.

The catchment area is subdivided into a wedge with 2 arms within each wedge. Each wedge has a district hospital at the apex. The hospital is linked to a regional hospital, 2 community health care centers, and 2 primary health care clinics in each arm. The intervention study districts in the Eastern Cape, Limpopo, and Mpumalanga are highlighted in red in Figure 1. The comparison facilities and the intervention facilities are in different districts to avoid contamination, and the former will not have the same apex district hospital as the intervention site. The comparison districts (Figure 1 in yellow) are not evaluated for objective 4.

**Figure 1 figure1:**
[figure not shown]
Mphatlalatsane intervention and comparison districts in the Eastern Cape, Limpopo, and Mpumalanga Provinces in South Africa. Produced by the Health GIS Centre of the South African Medical Research Council. Copyright ESRI 2016; ArcGIS Desktop: Release 10.4. Redlands, CA: Environmental Systems Research Institute.

### Study Design

We are conducting a mixed methods implementation science type 2 hybrid effectiveness design to study the intervention effect (objectives 1-3) and implementation (objective 4) during the COVID-19 pandemic. Given that the intervention facilities were preselected, the quantitative component will be implemented as a quasi-experimental controlled before-and-after study (nonrandomized assignment of the intervention and comparison groups) to measure the effect of a QI intervention implemented during the COVID-19 pandemic on maternal and neonatal outcomes. Data on the iMMR, neonatal mortality rate, and stillbirth rate will be analyzed from 2019 to 2021, including the time before and during the COVID-19 pandemic in South Africa (objective 1). Study data on maternal experiences of care (objective 2) and maternal and neonatal quality of care (objectives 3a and 3b) were collected between 2021 and 2022. Objective 4 data collection commenced in early 2020 and ended in August 2022.

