### Eligibility Criteria and Recruitment of Facilities

#### Overview

The intervention facilities were purposively identified by the National Department of Health (NDOH) as sites with MNH service performance and capacity below the national average in South Africa. In addition, the selected intervention sites reflect the clinical and referral pathways and represent both urban and rural settings. For objectives 2 and 3, the comparison districts were purposively selected to match the intervention districts in as many respects as possible, including iMMR, stillbirth rate, neonatal mortality rate, sociodemographic characteristics, service organization, and setting (rural, urban, and periurban), and to provide the NDOH standard of care. In total, 3 facilities (2 district hospitals and 1 regional hospital) in the comparison district were selected and matched to the intervention district based on the total number of births. Data collection for objectives 2 and 3 is conducted in 18 hospitals (15 district- and 3 regional-level hospitals). Objective 4b is being conducted in 15 hospitals, purposively selected from the 21 intervention facilities.

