#### Objective 3a

Data collectors took photographs or abstracted data from maternal records, which were then entered into the REDCap database. Facility audit of maternal records were conducted by an experienced nurse to measure adherence to the guidelines and implementation of care. Data were collected at a single time point within 1 week of delivery.

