#### Objective 2 and 3a

Literature on patient satisfaction in South Africa is scarce; in other studies, patient satisfaction varies from <50% to as high as 75% [25]. The impact of the intervention on patient satisfaction may likely be less compared with that before the COVID-19 era because of disruptions in service delivery. For the 18 facilities in the intervention arm and 18 facilities in the control arm, at a power of 80%, and an expected increase in patient satisfaction from 50% to 60%, given an intraclass correlation coefficient of 0.06, the number of pregnant women required is 102, with a total sample size of 1529 per arm in the pre- and postintervention periods.

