
### Statistical Analysis

#### Objective 1

The institution maternal and perinatal mortality indicators will be calculated using DHIS data. Trend in iMMR, neonatal mortality rate, and stillbirth rates (with SE bars) during the pre- and postintervention periods will be disaggregated by intervention arms. RR and 95% CI will be calculated along with data on confounding variables, such as antenatal care coverage before 20 weeks, delivery at health facility access by tar road, deliveries of female participants aged <19 years, and deliveries of female participants aged ≥19 years (derived from total deliveries and deliveries of female participants aged <19 years). The trends in mortality and stillbirths will be compared before the COVID-19 pandemic (January 2019-March 2020) and during the COVID-19 pandemic (April 2020-March 2021) and in the context of the COVID-19 waves. The baseline period (2017-2018) will also be provided. Observed numbers and rates will be determined monthly and quarterly across all 9 provinces in the country and overall. To compare the Mphatlalatsane Initiative intervention and control arm trends in mortality, an interrupted time series regression model using Poisson regression model with Newey-West SEs to account for autocorrelation and possible heteroskedasticity will be used.

#### Objective 2

This study will use quantitative descriptive analyses and exploratory factor analysis to examine associations between sociodemographic characteristics, childbirth characteristics, and maternal participants’ experience of health care quality and the health care facility during the antenatal to postpartum period.

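### Objectives 2 and 3 promise a before-and-after effect, but all data described for them were collected in 2021–2022, after both the Initiative and the pandemic had begun

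*Protocol article*

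**What the plan says.** **Aim.** The Abstract (Objective) says the evaluation will determine whether the Initiative "improves patients’ experiences (objective 2) and quality of care (objective 3". Study Aims and Objectives instead describes objectives 2 and 3 as asking whether experience and quality were changed by the pandemic. Table 1 describes objective 2 as the QI effect over time, within 2021 to 2022.

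**Design.** Study Design covers the intervention effect for objectives 1 to 3 and calls the quantitative component a controlled before-and-after study. Sample Size (Objective 2 and 3a) gives "1529 per arm in the pre- and postintervention periods".

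**Timing.** The Abstract (Methods) states "The Mphatlalatsane intervention commenced at the end of 2019". Intervention Dose collects dose data from September 2019 and puts the start about 6 months before March 2020. Study Design says that experience data and "maternal and neonatal quality of care (objectives 3a and 3b) were collected between 2021 and 2022". Results dates the 3934 interviews from 27 October 2021 to 8 July 2022. Data Sources calls the objective 2 survey a midline and places objective 3 collection at the end line, about June to August 2022.

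**Analysis.** For objective 2, Statistical Analysis names "quantitative descriptive analyses and exploratory factor analysis to examine associations between sociodemographic characteristics, childbirth characteristics" and experience of care. For objective 3 it gives a percentage care score.

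**Sites.** The National Department of Health chose the intervention sites as "sites with MNH service performance and capacity below the national average". For objectives 2 and 3, comparison districts were purposively matched on mortality and stillbirth rates, sociodemographic factors, service organization and setting, and facilities on number of births.

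**The concern.** A before-and-after effect needs a measurement from before. If every measurement for objectives 2 and 3 came after the Initiative started, a difference between arms cannot be separated from a difference that was already there. If every measurement also came after the pandemic started, nothing shows how experience or quality stood without it. The stated objective 2 analysis does not use study arm, so carried out as written it would answer a different question from the objective. A report could then claim improvement, or a pandemic effect, that the data cannot show.

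**Working it through.** **1. Timing.** Months from each stated start to each collection date (days divided by 30.44):

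| Collection date | From 1 Sep 2019 | From 31 Dec 2019 |
|---|---|---|
| 1 Jan 2021 (earliest possible under Study Design) | 16.0 | 12.1 |
| 27 Oct 2021 (first dated interview) | 25.9 | 21.9 |
| 1 Jun 2022 (start of end line) | 33.0 | 29.0 |

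On the loosest reading, collection starts at least 12 months after the Initiative began and about 9 months after the end of March 2020. No entry is pre-intervention or pre-pandemic.

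**2. Aim against analysis.** The aim compares intervention with no intervention. The objective 2 analysis relates experience to sociodemographic and childbirth characteristics. It names neither arm nor period, although comparison hospitals were enrolled.

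**3. The plan's sample size.** Inputs from Sample Size (Objective 2 and 3a): 50% versus 60%, ICC 0.06, 80% power, 18 facilities per arm, 102 women, 1529 per arm. No significance level is given there; I assume two-sided 5%.

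- Before clustering: n = [1.96 × √(2 × 0.55 × 0.45) + 0.842 × √(0.25 + 0.24)]² / 0.10² ≈ 388 per arm.
- Design effect with 102 women per facility: 1 + 101 × 0.06 = 7.06, so 388 × 7.06 ≈ 2739 per arm, not 1529.
- 18 × 102 = 1836, not 1529, whereas 15 × 102 = 1530. The plan's figures do not reproduce together.
- A comparison of arms at one period needs more than 388 × 0.06 = 23.3 facilities per arm, however many women each contributes. Eighteen per arm with 1529 women gives about 62% power.

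**4. Facilities actually described.** Eligibility Criteria and Results give 18 hospitals in total. Sample Size (Objective 3b) gives 3 in each intervention and control catchment area, that is 3 × 3 = 9 per arm.

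**5. Power of the comparison that remains.** I assume the 3934 interviews split equally.

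- Per arm 1967; per hospital 1967 / 9 = 218.6.
- Design effect: 1 + 217.6 × 0.06 = 14.05. Effective size: 1967 / 14.05 ≈ 140 per arm.
- Power: Φ[(0.10 − 1.96 × √(0.495 / 140)) / √(0.49 / 140)] = Φ(−0.28) ≈ 39%.
- With unlimited interviews the effective size cannot exceed 9 / 0.06 = 150 per arm, giving Φ(−0.22) ≈ 41%.

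These are normal approximations; a small-sample correction lowers them further.

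**The case against.** **Matching.** The below-average selection of intervention sites is not the whole story, because comparison districts were matched on several factors. This stands: matching should reduce imbalance. It does not replace a baseline, since no earlier experience or care score is described against which to check it.

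**An arm contrast may be specified elsewhere.** Comparison hospitals were enrolled, and a fuller analysis plan or Multimedia Appendix 1 may name the model. This stands as to model detail. The point is that the analysis the article does state for objective 2 does not match its objective. The promise in the Discussion to stratify by intervention and control follows remarks on the routine mortality data.

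**Some change over time can be studied.** Table 1 limits its wording to 2021–2022, and the Discussion plans to look at differences during and between COVID-19 waves. This stands: change within the window is estimable. Contrasts with the time before the Initiative or the pandemic are not.

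**Midline implies a baseline.** A baseline wave may have existed, but none is described and Study Design dates collection to 2021–2022. If one exists, the article should say so.

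Four stronger readings are tempting and not supported:

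- That all collection came at least 2 years after the start. For the first dated interview this holds only from September 2019; from the end of 2019 it is about 22 months.
- That "Data were collected at a single time point within 1 week of delivery" proves a single study wave. It more naturally describes when each woman's record was abstracted.
- That the bias can be put in points. With ICC 0.06 the between-hospital SD is √(0.06 × 0.25) = 12.2 points at 50% satisfaction, and √(0.06 × 0.9258 × 0.0742) = 6.4 points at the observed 92.58%. The documents do not say what fraction of an SD separates the arms, so no bias figure follows.
- That 15 district and 3 regional hospitals is impossible given "3 facilities (2 district hospitals and 1 regional hospital) in the comparison district were selected and matched". If 2 district plus 1 regional held in all six areas, the total would be 12 + 6. But three such comparison areas plus nine intervention district hospitals gives exactly 15 + 3. Table 2, which shows three regional hospitals, lists the objective 4b sample. The split by arm is unclear, not contradictory.

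**Conclusion.** The point holds. Objectives 2 and 3 are worded as effects of the Initiative in one place and of the pandemic in another, under a before-and-after design. All described data postdate both exposures, by about 22 to 26 months from the Initiative's start to the first dated interview. Neither effect can be estimated from the data described, and the stated objective 2 analysis does not use study arm.

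A post-intervention comparison with matched hospitals remains possible. It supports association only, and power is about 39% for the planned difference. That figure rests on ICC 0.06, 9 hospitals per arm, equally split interviews and a two-sided 5% test. The planned 10-point rise is itself a doubtful benchmark: pooled antepartum satisfaction of 92.58% leaves 7.42 points of headroom. The direction and size of any baseline imbalance are unknown.

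These are secondary end points, but the wording decides what may be concluded from two of the three effectiveness objectives, so it needs correcting.

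**What to change.** - Restate objectives 2 and 3 consistently as post-intervention comparisons of intervention and matched comparison hospitals. If a baseline wave exists, describe it instead.
- For these objectives, remove the pre/post wording from the sample-size paragraph and the pandemic-effect wording from the aims. Limit any statement about time to change within 2021–2022.
- State one arm contrast per outcome, allowing for clustering by hospital with a small-sample correction. Keep hospital-level covariates few, for example hospital level and province: with intercept and arm that is 1 + 1 + 1 + 2 = 5 parameters on 18 hospitals.
- Reconcile 18 facilities per arm in Sample Size with 18 in total elsewhere, and give the district/regional split by arm. If regional hospitals sit in one arm only, adjusting for level leaves the arm comparison resting on district hospitals alone.
- Report the achieved precision and conclude association, not improvement.

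The cost is wording and one simple model on data already collected. The claim becomes weaker, and with 9 hospitals per arm more interviews would not restore the power.
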